## Abstract

**Background:**

Type 2 diabetes mellitus (T2DM) imposes a substantial burden owing to its increasing prevalence and life-threatening complications. In patients who do not achieve glycemic targets with oral antidiabetic drugs, the initiation of insulin is recommended. However, a serious concern regarding insulin is drug-induced hypoglycemia. Hypoglycemia is known to affect quality of life and the use of health care resources. However, health economics and outcomes research (HEOR) data for economic modelling are limited, particularly regarding utility values and productivity losses.

**Objective:**

This real-world prospective study aims to assess the impact of hypoglycemia on productivity and utility in insulin-treated adults with T2DM from Ontario and Quebec, Canada.

**Methods:**

This noninterventional, multicenter, 3-month prospective study will recruit patients from 4 medical clinics and 2 endocrinology or diabetes clinics. Patients will be identified using appointment lists and enrolled through consecutive sampling during routinely scheduled consultations. To be eligible, patients must be aged ≥18 years, diagnosed with T2DM, and treated with insulin. Utility and productivity will be measured using the EQ-5D-5L questionnaire and Institute for Medical Technology Assessment Productivity Cost Questionnaire, respectively. Questionnaires will be completed 4, 8, and 12 weeks after recruitment. Generalized estimating equation models will be used to investigate productivity losses and utility decrements associated with incident hypoglycemic events while controlling for individual patient characteristics. A total of 500 patients will be enrolled to ensure the precision of HEOR estimates.

**Results:**

This study is designed to fill a gap in the Canadian evidence on the impact of hypoglycemia on HEOR outcomes. More specifically, it will generate productivity and utility inputs for the economic modeling of T2DM.

**Conclusions:**

Insulin therapy is expensive, and hypoglycemia is a significant component of economic evaluation. Robust HEOR data may help health technology assessment agencies in future reimbursement decision-making.

**International Registered Report Identifier (IRRID):**

PRR1-10.2196/35461

## Introduction

### Background

Diabetes imposes a substantial burden because of its increasing prevalence and life-threatening complications. According to Diabetes Canada, 1 in 3 Canadians is living with diabetes or prediabetes, among which type 2 diabetes mellitus (T2DM) accounts for 90% to 95% of cases [1]. Glycemic control is key to diabetes management, and several types of oral therapies have been approved for T2DM. In patients who do not achieve glycemic targets on oral antidiabetic drugs, initiation of insulin therapy is recommended [1]. However, a serious concern regarding insulin is drug-induced hypoglycemia [2]. Hypoglycemic events are a major obstacle to the achievement of glycemic targets and represent a challenge for both patients and physicians. The severity of hypoglycemia is defined by clinical manifestations ranging from mild symptoms to seizure and coma [2].

### Current State of Knowledge

Hypoglycemia is known to affect quality of life and the use of health care resources. However, health economics and outcomes research (HEOR) data for economic modelling are limited, particularly regarding utility values and productivity losses. O’Reilly et al [3] recently published data on health care costs associated with hypoglycemia based on the Canadian cohort of the International Hypoglycemia Assessment Tool study. Although relevant data on direct costs were provided, productivity losses were subject to recall bias (1-year recall) and were limited to absenteeism (excluding presenteeism and unpaid work). Regarding utility values, a highly cited literature review by Beaudet et al [4] identified utilities for 20 modeling complications associated with T2DM. For hypoglycemia, the review found only 1 study with utility estimates suitable for economic modeling, that is, considering the number of events (rather than the presence vs absence of hypoglycemia). Economic modeling of T2DM is particularly challenging because multiple interrelated organ systems are involved over a long period, with numerous risk factors. For an adverse event such as hypoglycemia, HEOR data should depend on the number of episodes to fit T2DM economic models, as in the study by Currie et al [5], the current preferred source for utility values for hypoglycemia. Although the study by Currie et al [5] is the source recommended by several health technology assessment (HTA) agencies, it is criticized by the National Institute for Health and Care Excellence (NICE) for being subject to selection bias and recall bias [6,7]. It should be noted that Beaudet et al [4] also highlighted that variability around the utility estimates (eg, SE) is not always reported, thereby limiting future sensitivity analyses in cost-utility analyses (CUAs).

Canadian data on productivity losses due to hypoglycemia include a 2005 survey of 133 patients with T2DM of whom up to 9% and 26% missed work or studies following nonsevere hypoglycemic events (NSHEs) and severe hypoglycemic events (SHEs), respectively [8]. A web-based survey included 150 patients with T2DM having a nocturnal NSHE in the previous month. Among the 87 working respondents, 15 (17%) reported an average of 3.5 hours of lost work [9]. In the Canadian Hypoglycemia Assessment Tool cohort, 6% (8/134), 3.8% (5/134), and 7.5% (10/134) of T2DM workers reported on average 2.9 days taken off (SD 21.2), 3.8 days arriving late (SD 8.8), and 1.7 days leaving early (SD 0.7), respectively, based on a 1-year recall [3]. As for utility, time trade-off (TTO) values were elicited from 51 Canadian respondents with diabetes and 79 respondents from the general population. The mean utility ranged between 0.85 and 0.94, 0.77 and 0.90, and 0.66 and 0.83 for rare hypoglycemic events (quarterly), intermediate (monthly), and frequent (weekly) health states, respectively. In a multivariate linear regression, the estimated utilities associated with a single hypoglycemic event (all types combined) were −0.0033 and −0.0032 for respondents with diabetes and the general population, respectively [10]. Another TTO study estimated utility decrements of 0.006, 0.008, 0.059, and 0.062 for daytime NSHEs, nocturnal NSHEs, daytime SHEs, and nocturnal NSHEs, respectively [11]. A third TTO study including patients with diabetes and respondents from the general population estimated utility decrements ranging from 0.0028 to 0.0056, 0.0076, 0.0592 to 0.0726, and 0.0616 to 0.0826 for daytime NSHEs, nocturnal NSHEs, daytime SHEs, and nocturnal SHEs, respectively [12]. No Canadian studies that met the Canadian Agency for Drugs and Technologies in Health (CADTH) recommendation to use an indirect method for utility measurement (eg, EQ-5D) were identified.

### Study Rationale and Relevance

The population at risk of drug-induced hypoglycemia is significant, with nearly 20% to 30% of patients with T2DM requiring insulin [13,14]. In the last 5 years, CADTH has reviewed 9 economic evaluations in T2DM, among which 3 were CUAs for insulin therapies [15-17]. Considering the growing interest in HEOR data in insulin-treated patients with T2DM, there is a need for robust estimates. Data on productivity losses are lacking, which are particularly meaningful in Quebec, where the *Institut national d’excellence en santé et en services sociaux* preconizes economic evaluations by adopting a societal perspective. In addition, in 3 recent pharmacoeconomic reports on insulin therapies for T2DM, CADTH highlighted the uncertainty around utility values for hypoglycemia [15-17]. The committee described the current evidence on the impact of hypoglycemia on utility as limited and of low quality. In CADTH’s reanalyses for the 3 CUAs, variation in utility values for hypoglycemia led to a significant change in the estimates of quality-adjusted life-years gains. The incremental cost-effectiveness ratios were very sensitive to any changes in utility decrements for hypoglycemic events and were therefore determined to be an important driver of the results [15-17]. Thus, there is a need for HEOR data that are robust enough to make an informed decision with reasonable uncertainty. The aim of this real-world prospective study is to assess the impact of hypoglycemia on productivity and utility in insulin-treated adults with T2DM from Ontario and Quebec, Canada.

## Methods

### Research Purpose and Study Design

This noninterventional, multicenter, 3-month prospective study is designed to collect HEOR inputs for future economic modeling. This study will generate descriptive HEOR estimates that can be incorporated into T2DM models, along with precision parameters (ie, CIs and SEs) to evaluate uncertainty in CUAs in sensitivity analyses. Considering the nature of the disease, a longitudinal design with repeated measures was deemed appropriate to limit confounding and increase the quality of evidence.

### Study Population

In Canadian clinical practice, patients with T2DM who are on insulin can be followed up by a family physician or a specialist [18]. Therefore, patients will be recruited from 4 medical clinics and 2 endocrinology or diabetes clinics. To increase generalizability, patients will be recruited from the 2 largest Canadian provinces, Ontario and Quebec. Patients will be identified using appointment lists and enrolled through consecutive sampling during routinely scheduled consultations. To be eligible, patients must be aged ≥18 years, diagnosed with T2DM, and treated with insulin. There are no restrictions on insulin regimens (eg, short-acting, long-acting, or mixed insulin). Given the lack of reimbursement, the use of insulin pumps is limited in the treatment of T2DM [19]. Patients must also be able to understand and read English or French and provide informed consent. Patients will be excluded if they participate in a clinical trial. A screening log will be used to document the participation rates.

### Definition of Hypoglycemia

According to the Canadian Diabetes Association and the American Diabetes Association (ADA), hypoglycemia is defined as plasma glucose concentrations of ≤3.9 mmol/L (≤70 mg/dL) [2,20]. To reflect a real-world setting, the definition of hypoglycemia in this study is not restricted to documented episodes but includes any hypoglycemic event as judged by the patient. Symptoms defining hypoglycemia include trembling, palpitations, sweating, anxiety, hunger, nausea, tingling, difficulty concentrating, confusion, weakness, drowsiness, impaired vision, difficulty speaking, headache, and dizziness. Patients will self-report hypoglycemic episodes recorded by either symptoms or blood glucose testing alone or a combination of both. This approach has also been used in several large real-world studies [18,19,21-24] and better represents real-life practice where patients do not always test their blood glucose level for different reasons (eg, forgetting, neglecting, lack of knowledge, or lack of testing materials). Hypoglycemic events will be categorized as either severe or nonsevere. An SHE is defined as an event requiring assistance from another person (to administer carbohydrates, to administer glucagon, or take other corrective actions), whereas an NSHE can be managed by the patient alone, as per the Canadian Diabetes Association and ADA definitions [2,20].

Along with the severity of hypoglycemic events, the frequency of events promotes the fear of future hypoglycemia [2,20]. Fear itself affects patients’ quality of life [2,20]. In addition to the physical symptoms due to hypoglycemic events, the negative emotional impact of the fear of hypoglycemia is also a concern. For modeling purposes, HTA agencies recommend that the assessment of the impact of hypoglycemia on utility should consider both the severity and frequency of episodes. They also recommend not applying a utility decrement separately for the fear of hypoglycemia. Therefore, this study was designed to capture the overall impact of hypoglycemia on utility, including the transient effects of events and the resulting fear.

### Measurement of Outcomes

#### Utility

The EQ-5D-5L questionnaire will be used to measure the utility values [25,26]. This validated instrument is widely used and covers five dimensions (mobility, self-care, usual activities, pain or discomfort, and anxiety or depression) that are further divided into five levels (no problems, slight problems, moderate problems, severe problems, and extreme problems). The EQ-5D (EQ-5D) health states may be converted into a single summary index through a crosswalk value set. An EQ-5D summary index of 1 represents complete health, 0 represents death, and negative values represent states worse than death. The questionnaire also includes a visual analog scale that records the respondent’s self-rated health using a vertical scale ranging from 0 to 100 with end points labeled as “the best health you can imagine” and “the worst health you can imagine.” EQ-5D scores represent patients’ health status on the day of questionnaire completion.

#### Productivity Loss

The Institute for Medical Technology Assessment (iMTA) of Erasmus University Rotterdam recently developed and validated a questionnaire to estimate productivity losses, referred to as the iMTA Productivity Cost Questionnaire (iPCQ) [27]. The *i*PCQ is a generic questionnaire designed to determine the value of productivity losses for economic evaluations adopting a societal perspective. The questionnaire included three modules: lost productivity at paid work because of absenteeism, lost productivity at paid work because of presenteeism (reduced productivity), and lost productivity at unpaid work. A recall period of 4 weeks is used for presenteeism and unpaid work. Absenteeism is divided into two categories: short-term absence (no longer than 4 weeks) and long-term absence (sick leave that started before the recall period).

### Study Procedures

#### Data Collection

The sociodemographic and clinical characteristics of the patients will be collected at recruitment. Patients will complete a baseline questionnaire to report their age, gender, ethnicity, education, income level, employment status, living status, alcohol consumption, smoking, and physical activity. As a proxy for frailty, the self-reported number of visits to a health care provider over the last 3 months and the number of emergency visits and hospitalizations over the last 6 months will also be collected [28]. As a proxy for lifestyle habits, immunization status (pneumococcal, influenza, and COVID-19) will also be self-reported. Self-care (disease management activities) will be assessed using the Diabetes Self-Management Questionnaire, a validated questionnaire covering behaviors related to glycemic control (diet, blood glucose monitoring, medication adherence, physical activity, and contact with health care professionals) [29]. The type of device used for glucose monitoring will also be recorded (eg, traditional finger-prick monitor and flash glucose monitoring device). It should be noted that continuous glucose monitoring systems are not reimbursed in T2DM, thereby limiting their use. To describe the history of hypoglycemia, patients will also be asked if they have experienced NSHEs and SHEs over the last 3 months and the last year, respectively. The duration of diabetes, glycated hemoglobin (HbA_1c_), BMI, therapy, duration of insulin, and vascular complications will be extracted from the patients’ medical records.

#### Assessments and Study Calendar

Patients will complete a self-assessment questionnaire (SAQ) at 4, 8, and 12 weeks to report the number of NSHEs and SHEs experienced in the last 28 days. Patients will also be provided with a diary to prospectively record hypoglycemic events. Both the SAQ and the diary will be used to estimate the number of hypoglycemic events. The EQ-5D and *i*PCQ will also be completed at 4, 8, and 12 weeks. The study calendar is shown in Figure 1. The questionnaires will be completed electronically via a web-based platform. To ensure that patients complete their questionnaires in a timely manner, reminders will be sent to them via email. Paper-based questionnaires can be provided to participants who do not have access to or are less familiar with using the internet (phone call reminders).

**Figure 1 figure1:**
[figure not shown]
Study calendar. iPCQ: institute for Medical Technology Assessment Productivity Cost Questionnaire; SAQ: self-assessment questionnaire.

### Ethical Considerations

This study will be conducted in accordance with the Declaration of Helsinki [30]. Approval will be taken from an independent review board before the initiation of the study, and each patient will have to provide written informed consent. After receiving independent review board approval, the protocol will be registered on ClinicalTrials.gov. All study documents, including validated versions of questionnaires, will be made available to participants in English or French, according to their preferences. The patients will not incur any costs for volunteering to participate in this study. Patients will receive a compensation of CAD $20 (US $15.75) for their participation after completion of each questionnaire.

### Statistical Analysis

#### Presentation of Results

Data will be screened for accuracy, and questionnaires completed in paper format (if any) will entail double data entry to minimize transcription errors. Baseline characteristics of all patients participating in the study will be presented. Categorical variables will be summarized as frequencies (number and proportion), and descriptive statistics (mean and SD) will be provided for continuous variables. Hypoglycemia will be measured as hypoglycemic events and treated as a continuous variable, as recommended by HTA agencies for economic modeling of T2DM [6,7]. If hypoglycemic events are reported at a higher rate in the patient’s diary than in the SAQ, diary values will be used to calculate the number of events, and SAQ values will be used in the sensitivity analysis. For the EQ-5D-5L, questionnaire scores will be calculated according to the EuroQoL scoring manual [31] using the Canadian crosswalk value set [32]. For the *i*PCQ, productivity losses will be calculated for each module (absenteeism, presenteeism, and unpaid work) using the iMTA scoring manual [33] and summed up to a total number.

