## Discussion

### Strengths and Limitations

Insulin-induced hypoglycemia is a burden to patients with diabetes, and this study will collect HEOR estimates reflecting how SHEs and NSHEs negatively affect patients’ productivity and utility. To our knowledge, this would be the first Canadian real-world study to attempt to longitudinally measure the impact of hypoglycemia on utility and productivity loss, including absenteeism, presenteeism, and unpaid work, in insulin-treated patients with T2DM. In this study, hypoglycemia will be categorized into SHEs and NSHEs without further subgrouping by severity (eg, mild or moderate) or time of occurrence (daytime or nocturnal). This classification is preconized by HTA agencies for CUAs in T2DM [6,7]. Subjective measurement of hypoglycemia may overestimate the number of episodes, which may underestimate the outcome values by event (conservative approach). In addition, the recently published guidelines by the International Hypoglycaemia Study Group recommend that the hypoglycemia threshold be lowered to <3.0 mmol/L (<54 mg/dL) in clinical trials [54]. This threshold was suggested because it is sufficiently low to indicate serious, clinically important hypoglycemia and because this level does not occur under physiological conditions in individuals who do not have diabetes. A joint position statement by the ADA and the European Association for the Study of Diabetes was subsequently published, which indicated that the glucose level should be lowered for clinical trials [54]. The use of the official definition of hypoglycemia (≤3.9 mmol/L) instead of a lower threshold might lead to overreporting of nonclinically serious events. Nevertheless, this approach is also conservative as it underestimates the outcome values by event. Defining hypoglycemia based on symptoms or blood glucose measurements is considered a reliable method that best reflects real-world practice [18,19]. The frequency of assessments (recall period) was based on previous Canadian studies [18,19]. The use of diary records (if higher than the number reported in the questionnaire) can compensate for potential recall bias and is a conservative approach as it would decrease the outcome values by event. Considering that longitudinal studies usually have a minimum of 3 measurements and that the frequency of assessments is 4 weeks, the duration of the study is therefore 3 months.

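### Counting events by the diary only when it exceeds the SAQ corrects recall bias in one direction only, and the result is not guaranteed to be conservative

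*Protocol article*

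**What the plan says.** Patients complete the SAQ at weeks 4, 8 and 12 "to report the number of NSHEs and SHEs experienced in the last 28 days" (Assessments and Study Calendar). The same section adds: "Patients will also be provided with a diary to prospectively record hypoglycemic events", and "Both the SAQ and the diary will be used to estimate the number of hypoglycemic events". The EQ-5D and the iPCQ are completed at the same three time points.

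Presentation of Results gives the rule for combining the sources. When the diary rate is higher than the SAQ rate, "diary values will be used to calculate the number of events, and SAQ values will be used in the sensitivity analysis". It gives no separate rule for the case where the SAQ is higher.

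Strengths and Limitations gives the justification: "The use of diary records (if higher than the number reported in the questionnaire) can compensate for potential recall bias and is a conservative approach", on the ground that more events mean a smaller value per event. The same section accepts that subjective reporting may overstate the number of episodes, and calls that conservative too.

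Independent Impact of Hypoglycemia makes the log-transformed count the exposure in the main model. The original scale is a sensitivity analysis.

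**The concern.** The source is chosen by its value. The diary displaces the SAQ only upwards, so the rule repairs forgetting but not over-recall. When a patient's SAQ includes events from before the 28-day window, the prospective diary shows the lower count and is set aside. The named sensitivity analysis does not expose this, because where the SAQ is higher the main and sensitivity counts are identical.

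The SAQ is also completed at the same time points as the outcomes, so over-recall may depend on how the patient feels when answering. The model covariates are treated as time invariant, apart from hypoglycemia and incident vascular complications, so adjustment would not remove such a link.

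The per-event utility decrement is the study's main product, and Study Rationale and Relevance says that cost-effectiveness ratios are very sensitive to it. A modeller who reads that the estimate is conservative will treat it as a lower bound on the harm. That reading is safe only if the direction of the error is known.

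**Working it through.** **1. The rule.** Write D for the diary count and S for the SAQ count in one comparison unit.
- D > S: main analysis uses D, sensitivity analysis uses S.
- D ≤ S: main analysis uses S, and the SAQ-based sensitivity analysis also uses S.

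The main count is therefore max(D, S). No named analysis uses D where D < S. The plan gives no figure for the effect of the rule, so there is none to reproduce.

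**2. The argument that more events mean a smaller value per event.** Inflate every positive count by 1.5.
- Original scale, true slope −0.005: −0.005 / 1.5 = −0.0033. The argument holds.
- Log scale, true coefficient −0.020: log(1.5x) = log(1.5) + log(x). The constant goes into the intercept and the coefficient stays −0.020. The argument does not carry over.
- Zero counts need an offset, which the article does not specify. With log(1+x) and gamma-Poisson counts (mean 2.0, shape 0.8, 37% zeros), the coefficient falls to about −0.017. That is some attenuation, but less than the one third on the original scale.

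**3. Recall error with and without a link to health.** The documents give no error rates, so all inputs are assumed. NSHEs: mean 2.0 per 28 days, shape 0.8, SAQ adds 0.5 over-recalled event. SHEs: mean 0.1, shape 0.3, SAQ adds 0.03. The diary and the SAQ each capture 90% of true events. Utility falls by 0.06 per SD of poorer health on the day, with residual SD 0.15. Over-recall is either unrelated to health or multiplied by exp(0.5u) or exp(1.0u), where u is poorer health in SD units (mean held fixed). There were 400,000 records per scenario. Entries are simple slopes divided by the true slope.

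| Scenario | Diary | SAQ | Higher of two |
|---|---|---|---|
| NSHE, log(1+x), unrelated | 1.00 | 0.93 | 0.95 |
| NSHE, log(1+x), related | 1.01–1.02 | 1.52–1.85 | 1.50–1.81 |
| NSHE, original, unrelated | 1.09 | 1.01 | 1.00 |
| NSHE, original, related | 1.05–1.07 | 1.44–1.80 | 1.38–1.71 |
| SHE, log(1+x), unrelated | 1.02 | 0.77 | 0.79 |
| SHE, log(1+x), related | 0.97–1.07 | 1.36–1.73 | 1.33–1.66 |

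If the SAQ only forgets (70% recalled, no over-recall), the higher-of-two NSHE count averages 1.86 against a true 2.0 and the ratio is about 1.03. In that case the rule does what it is meant to do.

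**4. True effect zero.** A second simulation on the original scale assumed a mean of 2.5 events, diary capture of 70–90%, and SAQ recall rising 10–20% per SD of feeling worse, with or without 25% extra pre-window events. Utility fell by 0.15 per SD of feeling worse. The higher-of-two count gave a false decrement of 0.0014–0.0036 per event, the SAQ alone 0.0017–0.0045, and the diary about 0. The planned SAQ check would therefore appear to confirm the artefact.

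**The case against.** **The wording is modest.** The Discussion says only that diary use can compensate for recall bias. For forgotten events that is right, and the text openly accepts over-counting. This stands: the justification is incomplete, not false.

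**The rule is no worse on slope than the SAQ alone.** In the second simulation with recall unrelated to health and a true decrement of 0.005, the SAQ alone gave 0.0036–0.0037 and the higher-of-two count about 0.0038. The loss comes from the assumed SAQ noise, not from the rule. On the log scale the higher-of-two count gave about 0.018 against 0.020, roughly 10% low. This stands, so a reader should not infer that the rule itself causes a 24% attenuation.

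**The diary's good result is built in.** The simulations let health affect recall but not diary-keeping. If patients who feel worse record less (assumed logit slope 0.3–0.6 per SD, true effect zero, SAQ unaffected), the diary gave −0.0027 to −0.0055 per event, an error in the opposite direction, against −0.0004 to −0.0008 for the higher-of-two count. The documents support neither assumption. A diary with 70% capture also overstates the per-event value by about 30% on the original scale. This stands, and it rules out a recommendation to make the diary the main source.

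**Over-recall need not always survive.** If the source is chosen per patient or for the whole study, SAQ excesses in single intervals are dropped whenever the diary rate is higher overall. This stands as well. The text does not fix the level.

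None of this answers the core point. The article itself names the rule, its one source check and its justification, so the gap is not a detail left to an unseen analysis plan.

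**Conclusion.** The concern holds in a limited form. The rule corrects under-recall only, the one source sensitivity analysis named cannot reveal SAQ over-recall, and the direction of bias is not guaranteed conservative. The first two points follow from the text, provided the SAQ count stands when it is the higher. The third follows from algebra for the log scale. It also depends on whether over-recall goes with poorer health, which the documents do not settle. If it does, the simulated log-scale overstatement was 1.3- to 1.8-fold. If it does not, the higher-of-two estimate was 5% low for NSHEs and 21% low for SHEs. These figures come from assumed error rates and simple slopes for utility, not from the planned adjusted GEE. They show direction only.

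Three stronger readings are tempting and are not supported. The documents do not show that over-recall is always kept, because the level of comparison is open. They do not show that the recall-bias justification is wrong, because it is sound for forgotten events. They do not show that the diary is the better main source, because under-recording carries its own bias. The similarity between the simulated false decrements and the smaller NSHE values cited under Current State of Knowledge reflects the chosen inputs and is not evidence.

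**What to change.** 1. State the level at which diary and SAQ are compared (per patient, per 28-day interval or overall), that SHEs and NSHEs are compared separately, and which count is used when the SAQ is higher.
2. Add a diary-only sensitivity analysis for all patient-periods with a returned diary. Report it beside an SAQ-only analysis for all patients, both on the log and on the original scale.
3. Reword Strengths and Limitations to say that the rule compensates for under-recall only and that its direction of bias is not guaranteed to be conservative.

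The main analysis can stay as it is. Both sources are already collected, so the cost is wording and one more sensitivity analysis. A diary-only count may miss unrecorded events, so it should be read together with the SAQ-only result. Agreement between the two would be reassuring, and a gap would show how much the estimate depends on the source.
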